## Abstract

**Background:**

The prevalence of low back pain increases with age and has a profound impact on physical and psychosocial health. With increasing age comes increasing comorbidity, and this also has pronounced health consequences. Whilst exercise is beneficial for a range of health conditions, trials of exercise for low back pain management often exclude older adults. It is currently unknown whether an exercise program for older adults with low back pain, tailored for the presence of comorbidities, is acceptable for participants and primary healthcare providers (PHCPs). Therefore, this mixed-methods study will assess the feasibility of an 8-week comorbidity-adapted exercise program for older people with low back pain and comorbid conditions.

**Methods:**

The 3-phased feasibility study will be performed in a primary healthcare setting. PHCPs will be trained to deliver a comorbidity-adapted exercise program for older people with low back pain and comorbidities. Healthcare-seeking adults > 65 will be screened for eligibility over telephone, with a recruitment target of 24 participants. Eligible participants will attend an initial appointment (*diagnostic phase*). During this initial appointment, a research assistant will collect patient demographics, self-reported outcome measurement data, and perform a physical and functional examination to determine contraindications and restrictions to an exercise program. During the *development phase*, PHCPs will adapt the exercise program to the individual and provide patient education. During the *intervention phase*, there will be two supervised exercise sessions per week, over 8 weeks (total of 16 exercise sessions). Each exercise session will be approximately 60 min in duration. A qualitative evaluation after the last exercise program session will explore the feasibility of the exercise program for participants and PHCPs. Progression criteria will determine the suitability for a fully powered randomised controlled trial.

**Discussion:**

This mixed-methods feasibility study will assess an exercise program for older adults with low back pain and comorbidities. Once assessed for feasibility, the exercise program may be tested for effectiveness in a larger, fully powered randomised controlled trial. This information will add to the sparse evidence base on appropriate options for managing back pain in older adults.

**Trial registration:**

Australian and New Zealand Clinical Trials Registry registration number: ACTRN12621000379819p (06/04/2021; https://www.anzctr.org.au/Trial/Registration/TrialReview.aspx?ACTRN=12621000379819p).

**Supplementary Information:**

The online version contains supplementary material available at 10.1186/s40814-022-01097-x.

## Background

Low back pain is the leading cause of disability worldwide, and the prevalence of low back pain increases over the lifespan with a peak prevalence observed around the ages of 80 to 89 years [1]. Low back pain has a profound impact on the physical and psychosocial health of an older adult. For example, one-fifth of older adults with low back pain cannot care for themselves at home or participate in family and social activities [2]. Additionally, one in every four people aged > 80 years will report moderate to severe low back pain, and people aged > 80 years are three times more likely to have high intensity low back pain than those aged 50–59 years [3]. Whilst numerous national guidelines suggest exercise as a first-line treatment for low back pain [4, 5], older adults with low back pain who visit a general practitioner are 50% less likely to be advised about exercise than younger patients [6].

Comorbid diseases are defined as “any distinct additional entity that has existed or may occur during the clinical course of a patient who has the index disease under study” [7]. Comorbidity may be the effect of medical diseases existing simultaneously, but independently of each other [8], or of diseases that may be related [9]. Research has shown that women with spinal pain were twice as likely to be overweight or obese, have diabetes, and nearly twice as likely to have pulmonary disease and cardiovascular comorbidity, than older women without spinal pain [10]. Furthermore, musculoskeletal conditions such as low back pain are associated with an increased risk of reporting multiple chronic health conditions [11]. Indeed, it is estimated that two-thirds of people aged over 65 years have two or more chronic health conditions [12]. The consequences of comorbidity in older adults include poorer prognosis and increased healthcare use [13]. For instance, with every additional (non-musculoskeletal) comorbidity, there is a 40% increase in the risk of developing persistent low back pain (*OR*: 1.4; 95% *CI*: 1.3 to 1.5) [14]. The widespread exclusion of participants with comorbidities in research is of great concern [15]. There is a need for future trials to evaluate the effectiveness of interventions for older adults who have low back pain and comorbidities.

Exercise has been shown to be beneficial for a wide range of conditions that are associated with ageing such as falls [16], frailty [17], and sarcopaenia [18], as well as comorbidities that co-occur with low back pain [19]. Yet, randomised controlled trials of exercise programs for acute and chronic low back pain often do not include older adults with comorbid conditions [20, 21].

Recently, a comorbidity-adapted exercise intervention was designed and tested for patients with knee osteoarthritis [22], showing that tailored exercise therapy provided significant improvements in pain and physical functioning, and that these improvements were of clinical relevance [23]. It is currently unknown whether an exercise program for older adults with low back pain, tailored for the presence of comorbidities, is acceptable for participants and primary healthcare providers (PHCPs) such as physiotherapists and chiropractors. Therefore, this mixed-methods study will assess the feasibility of a comorbidity-adapted exercise program for older people with back pain and comorbidities. Specific aims directly related to assessing the feasibility are as follows:Determine the ability to recruit eligible older participants and report the retention rate.Evaluate adherence to, and fidelity of, the comorbidity-adapted exercise intervention.Assess the collection and completion of outcome measure data, as well as report adverse events.Evaluate the acceptability of the exercise program to participants and PHCPs.

## Methods

### Design and setting

This protocol describes the design of a mixed-methods feasibility study of a COMorbidity-adapted Exercise program for low BACK pain in older adults (COMEBACK). The study will be conducted in a primary healthcare setting. Chiropractors and physiotherapists (PHCPs) with more than 5 years’ experience in back pain management and rehabilitation will deliver the exercise program. Four PHCPs will be trained in how to deliver the exercise program, via structured, in-person training prior to the development phase of the intervention. The study protocol conforms with the Standard Protocol Items: Recommendations for Interventional Trials (SPIRIT) guidelines [24], with the SPIRIT checklist as Supplementary material 1 Furthermore, as it has been recently shown that exercise interventions for low back pain are poorly reported [25], the intervention has also been reported as per the Template for Intervention Description and Replication (TIDieR) [26] (Supplementary material 2), and the exercise program will comply with the i-CONTENT tool [27]. The study results will be reported according to the CONsolidated Standards Of Reporting Trials (CONSORT) statement extension for pilot and feasibility studies [28]. The trial was registered with the Australian and New Zealand Clinical Trials Registry, reference number: ACTRN12621000379819p (06/04/2021; https://www.anzctr.org.au/Trial/Registration/TrialReview.aspx?ACTRN=12621000379819p. Ethical approval was granted by the Macquarie University Human Research Ethics Committee, reference number: 52021641028032. The trial resources are being funded by a Macquarie University Research Seeding grant; however, they have no role in study design, data collection, and analysis, interpretation of data, or writing of this manuscript.

### Recruitment

The study population is a convenience sample of adults aged 65 years or older who seek care for their low back pain in a primary healthcare setting. Older adults with low back pain will be invited to participate, via in-clinic posters in general practitioner, university, and PHCP clinics. The involvement of general practitioners in the recruitment process of participants in exercise interventions often needs to be supplemented by other recruitment methods [29], so social media posts will also invite community-dwelling older adults with low back pain to participate. Interested older adults will telephone a research assistant, who will screen for eligibility. If patients meet inclusion and exclusion criteria (Table 1), they will be asked to attend an initial appointment. At the appointment, the patient will be provided with a participant information form, and the study is explained verbally by the research assistant. If the patient is willing to participate, written consent will be obtained.

**Table 1 Tab1:** Inclusion and exclusion criteria

*Inclusion (satisfy all)*	*Exclusion (satisfy any)*
Aged 65 years or older	Patients with radiculopathy, evidence of nerve root compromise, and/or intermittent neurogenic claudication
Non-specific low back pain (within the boundaries of the thoracolumbar junction to gluteal folds) of less than 3-month duration	Patients with medically diagnosed fibromyalgia, a primary chronic pain condition^a^, peripheral neuropathy
Diagnosis of at least one of the target comorbidities: coronary heart disease, hypertension, type 2 diabetes, obesity, chronic obstructive pulmonary disorder, and depression	Diagnosis of serious pathology in the spine (such as fracture, malignancy or metastatic disease, cauda equina syndrome)
Bayliss measure of illness burden score of 3 or above for at least one of the target comorbidities	Physiotherapy or chiropractic treatment for their low back pain in the last 3 months
Sufficient comprehension of the English language to understand exercise instructions	Inability to participate in treatment, e.g. due to transport problems, or unable to mobilise independently
	Patients with an unstable health condition or at risk of a serious adverse event as evaluated by a medical specialist
	Patients with psychosis disorders, posttraumatic stress disorder, obsessive-compulsive disorder, attention-deficit hyperactivity disorder, autism, anorexia nervosa, and bulimia nervosa and patients with an abuse disorder

^a^A primary chronic pain is defined as chronic pain that cannot directly be ascribed to any disease of structural injury[30, 31]

### Participants

In determining the sample size for progression criteria for a pragmatic pilot randomised controlled trial, CTs using a red/amber/green approach, we used the estimation from Lewis et al. [32] with an upper limit red zone (unacceptable) of 45% and a lower limit green zone (acceptable) of 75% for the feasibility outcome protocol adherence (Table 2). The test is a 1-tailed test with suggested alpha (*α*) of 0.05 and beta (β) of 0.1 [32]. Therefore, our target sample size is 24 participants. Participants must have at least one of the following target comorbidities: coronary heart disease, hypertension, type 2 diabetes, obesity, chronic obstructive pulmonary disorder, and depression (diagnosed by a medical specialist). There will be no cost to participants to undertake the exercise program as part of the study.

**Table 2 Tab2:** The traffic light system for progression criteria of this feasibility study to randomised controlled trial

	Green	Amber	Red
**Trial recruitment**	Recruitment of 24 participants with low back pain and comorbidity within 3 months	Recruitment of 24 participants with low back pain and comorbidity within 3–6 months	Twelve participants with low back pain and comorbidity are *not* recruited within 6 months
	At least 75% retention of participants through follow-up	At least 50% retention of participants through follow-up	Less than 45% retention of participants through follow-up
**Protocol adherence**	At least 75% of participants complete more than half of the exercise program sessions	At least 50% complete more than half of the exercise program sessions	Less than 45% complete more than half of the exercise program sessions
**Outcome data**	At least 80% of participants do not find the outcomes so burdensome that they would not participate in the study again	At least 70% of participants do not find the outcomes so burdensome that they would not participate in the study again	Less than 70% of participants do not find the outcomes so burdensome that they would not participate in the study again
	At least 80% of data is not missing due to attrition or lost to follow-up	At least 50% of data is not missing due to attrition or lost to follow-up	A total of 25% of data is missing due to attrition or lost to follow-up
	Improvements in low back pain and function found clinically relevant by at least 50% of the participants	Improvements in low back pain and function found clinically relevant by at least 25% of the participants	Improvements in low back pain and function found clinically relevant by less than 25% of the participants
	Improvements in quality of life and illness burden by at least 50% of the participants	Improvements in quality of life and illness burden by at least 25% of the participants	Improvements in quality of life and illness burden by less than 25% of the participants
	No serious study-related adverse events during the study period	Less than five serious study-related adverse events during the study period	Five or more serious study-related adverse events during the study period

Green (go), where there are no concerning issues that threaten the success of the trial; amber (amend), where there are remediable issues, thereafter proceeding with caution; red (stop), when there are intractable issues that cannot be remedied

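### Table 2's progression rule gives no colour to a 6-month total of 12 to 23 recruits, nor (a smaller gap) to retention or adherence from 45% to just under 50%

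*Protocol article*

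**What the plan says.** The Feasibility measures section makes the predetermined progression criteria the primary outcomes and uses the colours of Table 2 to decide whether to proceed to a full randomised trial. The relevant cells of Table 2 (Participants section) are as follows.

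- **Recruitment.** Green: "Recruitment of 24 participants with low back pain and comorbidity within 3 months". Amber: "Recruitment of 24 participants with low back pain and comorbidity within 3–6 months". Red: "Twelve participants with low back pain and comorbidity are *not* recruited within 6 months".
- **Retention.** Green: "At least 75% retention of participants through follow-up". Amber has the same form with 50%. Red: "Less than 45% retention of participants through follow-up".
- **Adherence.** Green is 75% or more of participants completing over half the sessions. Amber: "At least 50% complete more than half of the exercise program sessions". Red: "Less than 45% complete more than half of the exercise program sessions".

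The sample-size text in the same section takes 45% as the upper limit of red and 75% as the lower limit of green for adherence, with a one-sided alpha of 0.05 and beta of 0.1, and arrives at 24 participants. The Table 2 footnote describes the colours in words only: no concerning issues, remediable issues, intractable issues.

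**The concern.** A progression rule fixed in advance should give every possible result one colour. Here green and amber recruitment both require the full 24, while red requires failure to reach half of that. Everything between is unassigned. On retention and adherence, amber and red are five percentage points apart.

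These criteria are the primary outcomes. If the result falls in a gap, the colour has to be chosen after the result is known, and fixing the criteria beforehand was meant to prevent that.

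**Working it through.** **1. The plan's own figure.** Inputs from the Participants section: p0 = 0.45, p1 = 0.75, one-sided alpha 0.05 (z = 1.645), power 0.90 (z = 1.282).

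n = [1.645 × √(0.45 × 0.55) + 1.282 × √(0.75 × 0.25)]² / 0.30² = (0.818 + 0.555)² / 0.09 = 20.95.

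With continuity correction: (20.95 / 4) × [1 + √(1 + 2 / (20.95 × 0.30))]² = 24.17, which agrees with the stated 24. So 45% is the red limit on which the design was built.

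**2. Recruitment cells listed by count at 6 months.**

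| Total at 6 months | Cell met |
|---|---|
| 0 to 11 | Red |
| 12 to 23 | None |
| 24 | Green if reached within 3 months, otherwise amber |

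If the red cell is read as a shortfall of twelve, red becomes 0 to 12 and the gap 13 to 23. The gap remains.

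**3. How likely the recruitment gap is.** The documents state no expected rate, so this is an assumption: Poisson recruitment at r per month, with mean 6r at 6 months and 3r at 3 months.

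- P(red) = P(X ≤ 11), X with mean 6r
- P(gap) = P(12 ≤ X ≤ 23), X with mean 6r
- P(green) = P(Y ≥ 24), Y with mean 3r
- P(amber) = the remainder

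| r per month | Red | No colour | Amber | Green |
|---|---|---|---|---|
| 1 | 0.980 | 0.020 | 0.000 | 0.000 |
| 1.5 | 0.803 | 0.197 | 0.000 | 0.000 |
| 2 | 0.462 | 0.537 | 0.001 | 0.000 |
| 3 | 0.055 | 0.844 | 0.101 | 0.000 |
| 4 | 0.003 | 0.470 | 0.526 | 0.001 |
| 5 | 0.000 | 0.115 | 0.866 | 0.019 |
| 6 | 0.000 | 0.014 | 0.885 | 0.101 |

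On a fine grid of rates, the gap is the single most likely result from about 1.95 to 3.94 per month. Below that range red is most likely; just above it, amber is.

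**4. Retention and adherence at n = 24.** 10/24 = 41.7% is red, 11/24 = 45.8% meets no cell, and 12/24 = 50% is amber. For enrolled totals from 12 to 24 the gap never holds more than one count, and at 12, 14, 16 and 18 it holds none.

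The binomial probability of exactly 11/24 is 0.161 at a true rate of 45%, 0.149 at 50%, 0.061 at 60% and 0.002 at 75%.

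**5. Table against sample-size text.** If red ends at 45%, amber starts at 45%. Table 2 starts it at 50%.

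**The case against.** The best defence is that the verbal definitions fill the gaps. The footnote reserves red for problems that cannot be remedied, and the Feasibility measures section says progression is ruled out only by such problems. A total of 18 recruits, or 11/24 adherent, could reasonably be called amber on that wording. This stands to the extent that the study team would not be without guidance. It does not close the gap: the words assign no colour to any given number, and applying them means judging after the result is seen. The gaps do not look like deliberate latitude either, since the rows for outcome burden, clinical improvement, quality of life with illness burden, and serious adverse events each join amber to red without a break.

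Three further limits are accepted.

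- A reader might infer that the gap is where slow recruitment will usually end. The documents do not support that. They give no rate, and the section on recruitment and retention says the study is meant to find out how long recruitment takes. At about 1.9 per month or fewer, which is also slow, red is the likelier result.
- A reader might count 12 of the 25 possible totals as uncovered and take this as a measure of risk. It is not, because the totals are not equally likely.
- A reader might give the two gaps equal weight. The second is at most one count and is very unlikely if adherence is at the plan's own acceptable level of 75%.

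The sample size of 24 reproduces and does not depend on either gap.

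**Conclusion.** The point stands as a defect in a stated decision rule. It is not a matter of detail left to another document, because the article prints the thresholds and they do not meet. The recruitment gap carries the weight. Its probability ranges from 0.02 to 0.84 over assumed Poisson rates of 1 to 5 per month, and exceeds one half only at about 2 to 3.9 per month. The gap itself depends on no assumption; only its probability does. The 45% to 50% gap is secondary: one count at full enrolment, together with an inconsistency between Table 2 and the limit used to size the study.

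**What to change.** Make the categories contiguous before results are known.

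- **Recruitment.** Green: 24 within 3 months. Amber: green not met, but at least 12 within 6 months. Red: fewer than 12 within 6 months. This keeps the existing red limit. The documents do not rule out a higher one; if the sponsor prefers that, amber must start where red ends.
- **Retention and adherence.** Green: 75% or more. Amber: 45% to below 75%. Red: below 45%. Apply these as percentages of the number actually enrolled. For 24 participants they give red 0 to 10, amber 11 to 17 and green 18 to 24, but these counts are illustrative only: with 20 enrolled, 75% is 15, not 18.

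Starting amber at 45% leaves the sample-size basis intact. Moving the red limit up to 50% in the design as well would not: the formula in the working, with p0 = 0.50 and a difference of 0.25, gives 30.4, or about 34 with continuity correction.

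The cost is rewording Table 2, plus any matching update to the registration and the ethics-approved protocol, since these criteria are the primary outcomes. No extra participants or data are needed.

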### Feasibility measures

Predetermined progression criteria are the primary outcomes for this study. A traffic light system of green (go), amber (amend), and red (stop) will be used to determine progression of this feasibility study to a fully powered randomised controlled trial (Table 2) [35]. The study will not be feasible to progress if there are intractable issues that cannot be remedied [35].

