### Exercise program-specific outcomes

At 4 weeks and 8 weeks, global perceived effect and patient satisfaction data will be collected. Patients will be asked to rate perceived effectiveness on a scale of 1–9, with a score of 1 meaning much better, 5 meaning no change, and 9 meaning much worse [47]. Participant satisfaction with treatment will be measured using the numerical rating scale (0–10), with higher scores indicating greater satisfaction [48].

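### Table 2's quality-of-life and illness-burden row counts any improvement, and its pain-and-function row has no collected item assigned to it, so neither light is properly fixed in advance

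*Protocol article*

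**What the plan says.** The section Feasibility measures states: "Predetermined progression criteria are the primary outcomes for this study". Table 2 (section Participants) gives the criteria as green, amber and red limits. Two of its outcome-data rows concern improvement.

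- **Quality of life and illness burden.** Green is "Improvements in quality of life and illness burden by at least 50% of the participants", amber is "Improvements in quality of life and illness burden by at least 25% of the participants" and red is "Improvements in quality of life and illness burden by less than 25% of the participants". The row gives no size of change and no score, and does not spell out whether both outcomes must improve in the same person.
- **Pain and function.** Green is "Improvements in low back pain and function found clinically relevant by at least 50% of the participants", with amber from 25% and red below 25%. The row does not say which item records that judgement.

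Table 4 lists the pain scale, Oswestry index, EQ-5D-5L and Bayliss measure at baseline, 4 and 8 weeks, and global perceived effect and satisfaction at 4 and 8 weeks. On global perceived effect, the section Exercise program-specific outcomes says: "Patients will be asked to rate perceived effectiveness on a scale of 1–9". It gives no cut-off and does not refer to Table 2. The Analysis section plans mean change from baseline to 8 weeks with SD and 95% CI, plus coding of the interviews. It defines no responder.

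**The concern.** Both rows fix a percentage of participants but leave open what a participant must do to be counted.

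For quality of life and illness burden, the wording taken literally counts a change of any size. The row directly above it asks for clinical relevance; this one does not. When nothing has truly changed, repeat measurement still moves many people's scores in the favourable direction, so the row can leave red without any benefit.

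For pain and function the problem is different. The row asks for a participant's judgement, several collected items could supply one, and none is named. A criterion described as predetermined then still needs a choice before it can be scored.

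At stake is whether these two lights tell the sponsor anything about progression. A light that is usually amber when nothing has happened, or that waits on an unstated cut-off, adds little to a go, amend or stop decision.

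**Working it through.** **The plan's own figure.** The section Participants derives the sample size from protocol adherence, with an "upper limit red zone (unacceptable) of 45% and a lower limit green zone (acceptable) of 75" per cent, one-sided alpha 0.05 and beta 0.1, and concludes that "our target sample size is 24 participants". The one-sample formula with null variance gives n = (1.645 + 1.282)² × 0.45 × 0.55 / 0.30² = 23.55, so 24. The figure reproduces and is not in dispute. It was set on adherence and does not address the improvement rows.

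**Inputs for the quality-of-life and illness-burden row.** From the document: n = 24; green at 50%, so 12 or more participants; amber at 25%, so 6 to 11; red at 5 or fewer. Assumed, because the document gives no figures: no true change, symmetric noise, 0% or 20% of people with an unchanged score (ties), and correlation 0 to 0.5 between the two change scores.

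**Chance that one person improves by noise alone.**
- One score: (1 − ties)/2, which is 0.50 with no ties and 0.40 with 20% ties.
- Both scores, lower end: 20% ties, independent, 0.40 × 0.40 = 0.16.
- Both scores, upper end: no ties, correlation 0.5, 0.25 + arcsin(0.5)/(2π) = 0.333.

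**Chance of each light.** X ~ Binomial(24, q); green is P(X ≥ 12), and amber or better is P(X ≥ 6).

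| Reading | q | Green | Amber or better |
|---|---|---|---|
| Each score separately, 20% ties | 0.40 | 21.3% | 96.0% |
| Each score separately, no ties | 0.50 | 58.1% | 99.7% |
| Both, independent, 20% ties | 0.16 | 0.01% | 17.4% |
| Both, independent, no ties | 0.25 | 0.7% | 57.8% |
| Both, correlation 0.5, no ties | 0.333 | 6.8% | 86.2% |

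**Sensitivity to ties.** Both instruments are built from 5-point items, so unchanged scores may be more common. With 40% ties the single-score rate is 0.60/2 = 0.30, giving green 3.1% and amber or better 77.1%. For both scores, independent, it is 0.30 × 0.30 = 0.09, giving green below 0.01% and amber or better 1.7%.

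**Direction of other influences.** The study has one arm. Table 1 requires low back pain of less than 3 months' duration and a Bayliss score of 3 or above on at least one target comorbidity. Natural recovery and regression to the mean could therefore raise q above the values used, with no treatment effect. The document gives no figure for the size of this.

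**Effect of a minimum change.** As an illustration on one score, requiring more than 0.5 SD of the change score gives q = 0.309, green 3.9% and amber or better 79.7%. Requiring more than 1 SD gives q = 0.159, green 0.01% and amber or better 16.9%. The minimum change therefore has to be chosen with the 25% cut in view as well as the 50% cut.

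**Pain-and-function row.** No arithmetic applies. Table 2 needs a participant's judgement of clinical relevance. The candidates are global perceived effect (one overall 1-9 rating), satisfaction (0-10) and the 8-week interviews. None is linked to the row and none has a cut-off. The planned mean changes cannot yield a share of participants.

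**The case against.** The best case for the plan has four parts.

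1. *Responder definitions are detail for the analysis plan, which is not shown.* This stands in part. The choice of EQ-5D-5L score or the handling of missing values could sit there, and the article does give instruments, assessment times and an 8-week change. But the article itself states the row as a primary criterion, with exact percentages and no minimum change, and that rule misleads if followed as written.

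2. *The row joins the two outcomes with an and, so both must improve.* This is the natural reading, and on it green by noise is rare (0-7%). A reader might infer that both the 50% and the 25% cut lie at or below what noise produces; for the green cut under this reading that is wrong. Improvement on either score alone would give higher figures still, but the wording does not support that reading. The amber limit remains easy to reach in most of the cases shown, though not where ties are common.

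3. *Participants' views are collected.* This is right. A reader might infer that no data exist for the pain-and-function row, or that global perceived effect is the only participant judgement recorded. Neither holds: satisfaction and interviews are collected too. What is missing is the link and the cut-off. Nor does the document say that a definition will be picked after the data are seen; it only leaves that open. How far the responder share would move between definitions cannot be derived from the document, which gives no expected changes or SDs.

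4. *Amber means amend and proceed with caution, and these are two of eight rows.* This stands. No passage lets one row alone trigger progression, which limits the consequence.

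**Conclusion.** The concern holds in a limited form. With no true change, the quality-of-life and illness-burden row would be amber or better 96-99.7% of the time and green 21-58% if each score is counted separately. If both must improve, it would be amber or better 17-86% and green 0-7%. These figures rest on n = 24 from the document and on assumed symmetric noise, 0-20% ties and correlation 0-0.5. More ties would lower them; recovery and regression to the mean could raise them. The pain-and-function row cannot be scored from the article, because no collected item is assigned to it. The rows should be repaired before they are used for progression, but the sample size and the other criteria are untouched by this point.

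**What to change.** - **Pain and function:** score the row from the 8-week global perceived effect, as the share of participants at or below a score fixed in advance.
- **Quality of life and illness burden:** name the EQ-5D-5L score, set a minimum change above measurement error on it and on the Bayliss total, and state that both must be met. The document holds no measurement-error figures, so the source of each minimum should be given.
- **Denominator:** state it for both rows, including how participants without 8-week data are counted.
- **Alternative:** report both rows descriptively and take them out of the traffic lights.

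The cost is protocol wording; no new data are needed. There are two downsides. Fewer participants will count as improved. Global perceived effect is an overall rating and not specific to pain and function, so it answers that row only approximately.
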